## Methods: assignment of interventions

### Randomization and matching

After checking for all inclusion and non-inclusion criteria by the study investigator, patients will be randomized to either of the study arms (intervention or TAU). Allocation concealment will be guaranteed as the randomization will not be released until the participant has been recruited into the trial, taking place after all baseline measurements have been done.

Randomization will be performed by the Clinical Research Unit of the Department of Medical Information of the Montpellier University Hospital. Randomization will be stratified by study center. It will be centralized, accessible online, and programmed using the data Capture Software System (EnnovClinical randomization module) according to a minimization algorithm with a 1:1 ratio. The trial manager will be responsible for setting up and testing the randomization process, incorporating stratification by study center using random blocks 1:1, assuring that study groups of approximately the same size will be produced.

The patient number will be automatically generated by EnnovClinical software.

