### Study design and setting

This ENERGY trial is a two-arm study (ENERGY intervention versus TAU), single blind randomized and controlled clinical trial designed to assess the efficacy of an individual cognitive and behavioral therapy in patients with schizophrenia. We adhered to the Consolidated Standards of Reporting Trials (CONSORT) guidelines in the design of the trial.

Patients meeting all of the inclusion criteria and none of the exclusion criteria will be invited to participate in the study. After signing the informed consent form, they will be randomized into one of the two study arms: ENERGY intervention or TAU.

They will be assessed at baseline over a 1-week period for fatigue, global functioning, symptomatology, sleep, cognitive functioning, and antipsychotic medication. Blood samples will be collected. Patients will be re-assessed 3 months later (corresponding approximately to the end of the ENERGY intervention; if the intervention is delayed, this intermediate assessment will be performed as soon as the intervention is completed and within 15 days of the end of the intervention) and 9 months later (approximately 6 months after the intervention with a delay of 15 days maximum) for fatigue, symptomatology, global functioning, sleep, cognitive functioning, and antipsychotic medication. Blood samples will be collected at each of these assessment times.

This study is multi-centered and will be carried out in 9 of the 10 centers participating in the French national network of schizophrenia expert centers (FondaMental Foundation). Each center will recruit patients to both groups and therefore perform the ENERGY intervention. The following centers will be participating in this study:
Hôpital la Colombière, Centre Hospitalier Universitaire (CHU) de MontpellierCHU de Clermont FerrandHôpital Albert Chenevier, CréteilHôpitaux Universitaires de StrasbourgHôpital Sainte Marguerite, MarseilleHôpital Louis Mourier, ColombesHôpital le Vinatier, LyonCentre Hospitalier Alpes IsèreHôpital Charles Perrens Bordeaux

This study protocol has been reported in accordance with the “SPIRIT 2013 Checklist: Recommended items to address in a clinical trial protocol and related documents” (Additional file 1).

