#### Primary outcome measures

The primary outcome measure is the score at the Multidimensional Fatigue Inventory (MFI) [29]. The MFI is a self-assessment instrument with 20 items including 5 dimensions: General, Physical, and Mental Fatigue; Reduced Motivation; and Reduced Activity. It was validated in 93 patients with schizophrenia spectrum disorders. The test–retest showed a correlation between .66 and .91 for all subscales of MFI. The internal consistency was .92. The analysis of convergent construct validity showed a correlation of .68 (time 1) and .77 (time 2). No item was systematically identified as being difficult to answer [30].

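### The protocol describes one randomisation as both minimisation and random blocks, and two sections disagree on whether baseline comes before or after allocation

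*Protocol article*

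**What the plan says.** **Algorithm.** Protocol article, Randomization and matching: "Randomization will be stratified by study center". The allocation is central and online, and the module works "according to a minimization algorithm with a 1:1 ratio". The next sentence makes the trial manager responsible for setting up the process, "incorporating stratification by study center using random blocks 1:1". Centre is the only factor named.

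**Timing.** The same section withholds the allocation until the participant has been recruited, with randomisation "taking place after all baseline measurements have been done". Study design and setting gives another order: "After signing the informed consent form, they will be randomized into one of the two study arms". Its following paragraph opens: "They will be assessed at baseline over a 1-week period for fatigue".

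**Outcome.** Primary outcome measures: "The MFI is a self-assessment instrument with 20 items". Main endpoint analysis takes the change in this score from inclusion to 9 months and names inclusion and randomisation as a single time point. Justification of the study design accepts that patients receiving the therapy cannot be blinded.

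**The concern.** Minimisation chooses each arm from the running imbalance at the time a patient is entered. Permuted blocks follow a list generated in advance within each stratum. The text describes no hybrid, so a programmer could not tell which to build and a reader of the final report could not tell which was used.

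The order of baseline and randomisation has the greater statistical consequence. If a site followed the design section, patients could fill in the baseline Multidimensional Fatigue Inventory (MFI) already knowing whether they would receive therapy. Blinded assessors cannot protect a questionnaire that the patient completes. The baseline value is half of the change score, so a reaction to the allocation would enter the primary comparison directly.

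**Working it through.** **1. The plan's own figure.** Determination of sample size gives a difference of 2 points, SD 4, alpha 0.05 and 73 per group. Power is printed as .085 and is read here as 0.85; the test is taken as two-sided.

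- Normal approximation: n = 2 × (1.960 + 1.036)² × 4² / 2² = 71.8, so 72 per group.
- Noncentral t: power is 0.846 at 72 and 0.851 at 73.

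The figure of 73 is reproduced. Neither contradiction affects it.

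**2. The statements side by side.**

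| Item | Randomization and matching | Study design and setting |
|---|---|---|
| Algorithm | Minimisation, 1:1; also random blocks by centre, 1:1 | Not given |
| Order | Baseline complete, then randomisation (explicit) | Consent, randomisation, then a 1-week baseline (order of narrative) |

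The algorithm conflict lies within one section. The timing conflict is between an explicit rule and a sequence of paragraphs.

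**3. What a baseline shift would do.** Read delta as the simple difference, which is how the sample-size section treats it. If knowledge of the arm moves the mean baseline in one arm by b points, the between-arm difference in change moves by b. As a share of the planned effect this is b/2. The standard error at 73 per group is 4 × √(2/73) = 0.662, using the plan's SD of 4 for the analysed difference. The values of b are assumptions.

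| Assumed b (points) | Share of the 2-point effect | Power if the bias works against therapy | Two-sided type I error with no true effect |
|---|---|---|---|
| 0 | 0% | 0.86 | 0.05 |
| 0.25 | 12.5% | 0.75 | 0.07 |
| 0.5 | 25% | 0.62 | 0.12 |
| 1 | 50% | 0.33 | 0.33 |

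Power is from the normal approximation with effect 2 − b. Type I error is from the same approximation with the test statistic centred at b/0.662. In the baseline-adjusted second analysis the shift is multiplied by the regression slope on baseline, so with a slope below 1 the bias is smaller but does not vanish.

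**4. Does the choice of algorithm change predictability?** Block size and any minimisation probability are not given, so this is illustration only. Suppose someone in a centre of 20 knows all earlier allocations there and always guesses the arm with fewer patients. The rates are from 10,000 simulated runs.

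| Scheme (assumed) | Correct guesses |
|---|---|
| Simple randomisation | 50% |
| Blocks of 6 | 67% |
| Minimisation on centre, probability 0.8 | 68% |
| Blocks of 2, 4 and 6 mixed | 70% |
| Blocks of 4 | 71% |
| Minimisation on centre, no random element | 75% |

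Two of these can be checked by hand. Without a random element every second allocation is forced: (0.5 + 1)/2 = 75%, exactly as for blocks of size 2. For blocks of 4: (1/2 + 2/3 + 2/3 + 1)/4 = 71%. The restricted schemes lie between 67% and 75%, so predictability gives no strong reason to prefer blocks to minimisation.

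**The case against.** Randomization and matching is explicit that baseline comes first. The design section is an overview whose next paragraph carries no word such as then, and the visit schedule in Fig. 1 could not be checked. Eligibility must be confirmed before randomisation and requires an MFI score of at least 10, so one MFI score necessarily exists before allocation. The shift of 0.25 to 1 point has no source in the documents, in size or in direction. Much of this stands. The timing conflict may be loose drafting, and the risk is small if the eligibility score serves as baseline. The text does not say that it does, however, and the two orders still disagree as written.

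A reader might infer three stronger things.

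- *That the timing conflict breaks allocation concealment.* It does not. Allocation is central and online, and measuring baseline late does not reveal an upcoming assignment. What remains is predictability within a centre, which exists under either algorithm. It also depends on whether those who enrol know earlier allocations. The Blinding section covers assessors and analysts, and the protocol is silent on the enrolling physicians.
- *That half of all allocations, 100 of 200, are predictable.* This needs minimisation on centre alone with no random element, which behaves like blocks of 2. Such parameters may properly sit in a restricted document, so their absence from an article shows nothing.
- *That only blocks are acceptable.* The comparison of schemes does not support that.

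**Conclusion.** Both contradictions are in the current text. The algorithm is named in two incompatible ways, and the order of baseline and randomisation is given in two ways. The second matters more, because a self-reported baseline in unblinded patients is part of the primary endpoint. Its possible size, 12.5% to 50% of the planned effect, rests on three assumptions: that a site follows the design section against the explicit rule, that the eligibility MFI is not the baseline score, and that knowing the arm shifts the mean by 0.25 to 1 point. It illustrates what is at risk and does not estimate a bias. The sample size of 73 evaluable per group is unaffected. The point should be fixed, as a consistency correction that also protects the primary endpoint.

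**What to change.** 1. Name one algorithm in Randomization and matching: either centre-stratified blocks of varying size withheld from sites, or minimisation with a random element. Keep block sizes or the allocation probability in a restricted document.
2. Rewrite Study design and setting to match: consent, full baseline (MFI, the 1-week pedometer period, bloods and the other assessments), then randomisation. State whether the eligibility MFI is the baseline score.
3. Set the online module to release the allocation only once the baseline MFI is locked.
4. If recruitment has started, use the e-CRF audit trail to check the order of MFI entry and randomisation at each centre.

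The cost is a few sentences and one software setting. No delay is added, because Randomization and matching already requires baseline first. Once patients have been randomised before baseline, the order cannot be repaired for them, so the change is best made before enrolment.

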### Blinding

The psychologists performing inclusion, 3-month, and 9-month assessments will be blind to the allocations of the patients to either study arms of the randomized controlled study (RCT). Patients and psychologists performing the ENERGY therapy will be asked to avoid telling the assessor to which group they/the patient belongs to. A psychologist, blind to the randomization process, will perform the assessments, and another psychologist will perform the therapy interventions. Participants will be asked to not reveal their group allocation to the assessors. The data analysts that will be performing the analyses at the conclusion of the trial will also be blinded as to what group the data corresponds to. Unblinding should occur only in exceptional circumstances in case of any adverse events (AE) which will be reported immediately to the investigator.

## Methods: data collection, management, and analysis

### Data collection

Several scales and tests used in this study are comprised within the standardized evaluations performed in the schizophrenia expert centers and are therefore already used on a daily basis in the centers implicated in the study. Each year, all the members of the centers attend quotation sessions in order to ensure inter-rater validity.

For the scales specific to this study (MFI, CAINS, IMI-SR, IHSS, BQ, SCI, IPAQ), we will organize training sessions before the beginning of the protocol in the French expert schizophrenia Network. In addition, all schizophrenia expert centers meet monthly in Créteil, in a meeting organized by the FondaMental Foundation and have specific expertise in clinical, neuropsychological, and biological evaluation in schizophrenia. All teams will be trained in the intervention the year before the beginning of the study to guarantee the homogeneity and quality of treatment across the centers.

Data will be collected or reported in an electronic case report form (e-CRF) developed using the software Capture System EnnovClinical to control for data quality at entry. The connection is via a username and password unique to each specific user and giving access only to the data of the centers’ user. An audit trail function is included allowing a supervision and traceability of all actions from all users.

Concerning biological evaluations, we will have access to specialized platforms for Microbial translocation and inflammatory and immunologic dosing, localized in Nîmes and Montpellier allowing great communication with the study coordinator based in Montpellier.

Once a participant has been enrolled and randomized into their study arm, the study site will put in place every effort to follow the participant throughout the course of the study. In order to improve adherence and prevent loss to follow-up, we will organize phone calls and/or emails that will be sent before the intervention to recall patients of their appointments. Patients will be already following day hospital care, which we believe will also increase adherence to the study. Furthermore, each evaluation will be planned in accordance with each patients’ schedule, and all patients will be phoned 24 h before their evaluation to remind them of their appointment.

If a patient misses their appointment, the psychologist will call him/her. All attempts will be documented in the patient’s medical records. In case of discontinuation, the investigator will perform all examinations scheduled for the final study visit, which includes recording of AEs. In any case, the patient will be treated in accordance with standard care in the center.

Investigators should make every effort to minimize the number of patients lost to follow-up and to obtain a maximum of information on patients lost to follow-up, particularly in the search for any AEs.

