### Eligibility criteria

#### Inclusion criteria

Patients eligible in participating in this study must comply with the following criteria:
Age between 18 and 60 years.Signature of informed consent form. If patients have a tutor, they will have to sign the informed consent form too.Patients with a diagnosis of schizophrenia according to the Diagnostic and Statistical Manual of Mental Disorders 5 (DSM 5) established and validated by the study center’s investigating psychiatrist.Patients with a score at the “Multidimensional Fatigue Inventory” (MFI) greater or equal to 10.Patients with a follow-up in a day hospital at inclusion.Subjects must be able to attend all scheduled visits and to comply with all trial procedures.Participation of the patient must be noted in their medical files.Subjects must be covered by public health insurance.

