### Justification of the study design

This clinical trial is designed to assess the efficacy of an individual cognitive and behavioral therapy in patients with schizophrenia by comparing results from the ENERGY intervention to TAU.

We chose a single blind study to ensure that the psychologist performing the evaluations will be blinded to the randomization arm. It is not possible for patients following the ENERGY intervention to be in a blinded condition.

For the comparison group, called “treatment as usual” (TAU), no definition of classical usual care for patients with schizophrenia exists; the only consensus is that antipsychotic medication is essential [20, 21]. Furthermore, French data show a high rate of care in day hospitals for patients suffering from schizophrenia, with day hospital care accounting for 40% of outpatient care [22]; 84% of French sectors have at least 1 day hospital [23]. So, the TAU could be defined by antipsychotic medication coupled with day hospital care.

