### Statistical analysis

The statistical analysis plan (SAP), covering all the analyses to be performed on all data, will be written before database lock for final extraction.

For all collected variables, descriptive statistics will be shown for both study arms in order to verify the initial comparability of the groups. For metric variables, a check as to whether the data can be assumed to be normally distributed will be first conducted. For normally distributed variables, means and standard deviations will be calculated, whereas for skewed variables, medians and ranges will be given. For categorical variables group proportions and contingency tables will be prepared.

All tests of efficacy will be conducted on an intentions to treat (ITT) basis using, in case of missing data, the Last Observation Carried Forward method, and/or multiple or mean imputation [50]. A per protocol sensitivity analysis will also be performed taking into account only patients who completed the whole study without any major protocol deviations. This will enable us to reinforce the stability of results obtained by ITT approach.

Significance level will be set at *p* < 0.05. All statistical analyses will be performed using SAS software (SAS Institute, Cary, NC, USA).

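### The final-visit examinations of patients who discontinue are assigned to the investigator, whom the protocol does not require to be blinded, so rated secondary scales could be scored without blinding in those patients

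*Protocol article*

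**What the plan says.** Two sections of the protocol article make a blinded psychologist the basis of the design. Justification of the study design states: "We chose a single blind study to ensure that the psychologist performing the evaluations will be blinded to the randomization arm". Blinding repeats it: "The psychologists performing inclusion, 3-month, and 9-month assessments will be blind to the allocations of the patients", and again, "A psychologist, blind to the randomization process, will perform the assessments, and another psychologist will perform the therapy interventions". That section names one further blinded role: "The data analysts that will be performing the analyses at the conclusion of the trial will also be blinded". It names no others.

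Data collection then sets a different rule for patients who leave: "In case of discontinuation, the investigator will perform all examinations scheduled for the final study visit". The sentence goes on to say that these examinations include adverse event recording, so they are not limited to safety.

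The investigator is not the assessor. Under Inclusion criteria the diagnosis is "established and validated by the study center’s investigating psychiatrist", and Trial governance and monitoring describes psychologists who assist the investigators.

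On missing data, Statistical analysis says: "All tests of efficacy will be conducted on an intentions to treat (ITT) basis using, in case of missing data, the Last Observation Carried Forward". The same sentence then allows multiple or mean imputation, in addition or instead. Secondary endpoint analysis says that the secondary outcomes are handled much as the main one is.

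Blinding ends with: "Unblinding should occur only in exceptional circumstances in case of any adverse events (AE) which will be reported immediately to the investigator".

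**The concern.** Patients and therapists know the arm, so the blinded rater is the only protection that the design claims for observer-rated scales. If another role does the rating when a patient leaves, that protection lapses in a selected group. Leaving may be related to arm, because only the ENERGY arm has a course of 14 sessions to stop. Any rater leniency or severity linked to arm would then bias the comparison on the scales behind the secondary hypotheses on negative symptoms, amotivation and depression.

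The unblinding sentence raises a smaller point. It joins a restriction to exceptional circumstances with a trigger of adverse events of any kind, and it does not say who would be unblinded.

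**Working it through.** **1. Who rates.** Blinding gives the inclusion, 3-month and 9-month assessments to the blinded psychologist. Data collection gives the whole final-visit set of a discontinuing patient to the investigator. No other section says that the psychologist still does the rated scales in that case, so the two sections conflict as written.

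**2. Is the investigator blinded?** The article does not say either way. These sections bear on it:
- Randomization and matching: the investigator checks eligibility. Allocation is centralized and online, and the text does not say who sees the result.
- Trial governance and monitoring: physicians follow patients throughout the study.
- Medical history: drug therapy and psychosocial interventions are recorded at each visit. ENERGY is such an intervention, although the section does not say who records it.
- Collection of AEs and Notification of SAEs: reports cover the event's relationship to study treatment and any action taken with therapeutic interventions, and the investigator judges the causality of serious events.
- Blinding: patients and therapists are asked not to disclose the arm to the assessor. Nothing extends this to the investigator.

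Knowledge of the arm is therefore plausible and nothing prevents it, but it is not stated.

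**3. Can the exit rating reach the analysis?** It can. Under last observation carried forward it would be the last observation. If it were entered as the final visit, nothing would be left to impute. No section excludes it. Because other imputation methods are also listed, its use is possible but not fixed.

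**4. Which outcomes?** Primary outcome measures describes the MFI as self-assessed, so the identity of the examiner does not change who scores it. Symptomatology describes the CAINS as a semi-structured interview, and the PANSS and CDSS are symptom rating scales. The article does not say who rates the FROGS, so it is left out here.

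**5. How large could it be?** Inputs from the sample size section: 100 recruited per group and 15–20% loss over 9 months. The section's 73 per group reproduces for a difference of 2, SD 4, two-sided 0.05 and power 0.85, reading the printed .085 as 0.85: the t-test calculation gives 72.8, rounded up to 73. That figure has no bearing on this point.

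- Ceiling on exit ratings: 0.15 × 200 = 30 to 0.20 × 200 = 40 patients, or 15–20 per arm. Patients truly lost have no exit visit, so the real number is lower by an unknown amount.
- Illustration: shift in one arm's mean = d × a × b, where d is the share leaving, a the share of those who have the exit examination, and b the rater shift in SD units, present in one arm only. Both a and b are assumptions.
- With a = 1: 0.15 × 0.2 = 0.03 SD to 0.20 × 0.8 = 0.16 SD.
- With a = 0.5: 0.15 × 0.5 × 0.2 = 0.015 SD to 0.20 × 0.5 × 0.8 = 0.08 SD.
- With no rater shift, or an equal shift in both arms at equal rates of leaving, the contrast does not move.

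**The case against.** The best defense is that Blinding states a general rule covering the 9-month assessment, and that having the investigator perform the examinations may only mean site responsibility, since psychologists assist the investigators on site. That reading is arguable. But the sentence assigns the examinations to the investigator without reference to the assessor, and a site following it literally would bypass the blinded rater.

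Three further objections are sound and limit the point:
- A reader might infer that the investigator is unblinded and scores knowing the arm. The article does not say so. A clause on unblinding for adverse events that mentions reporting to the investigator could even suggest a role that does not routinely know the arm.
- A reader might infer that any adverse event can break the blind. The sentence restricts unblinding to exceptional circumstances. It is loosely drafted but is not an open door.
- A reader might infer that exit ratings will be carried into the analysis. Carry-forward is one of several listed methods.

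The reach is also modest. The primary outcome is untouched, and Secondary endpoint analysis calls the clinical measures exploratory, although Hypotheses names negative symptoms and depression among the secondary hypotheses.

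**Conclusion.** The point holds as a conflict between sections. The discontinuation examinations are given to a role that the protocol does not require to be blinded and that plausibly knows the arm, while the design rationale depends on a blinded rater. The consequence is a possible rater bias in observer-rated secondary scales among patients who leave. The primary analysis is not affected by this route.

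The documents give no size. At most 30–40 of 200 patients are involved, and the illustrative range of 0.03–0.16 SD needs every one of them to have an exit rating that is used in the analysis, together with an assumed one-arm rater shift of 0.2–0.8 SD. It is tempting to express such a shift as a share of a 0.5 SD effect, but that effect (2/4) is planned for MFI general fatigue, which this route does not touch. The sample size section gives no effect size for the PANSS, CAINS or CDSS, so no percentage is supportable.

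The wording of the unblinding sentence is a minor drafting matter.

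**What to change.** In Data collection, state that at discontinuation the blinded assessing psychologist performs the rated scales of the final-visit set, and that the investigator records adverse events and the reason for discontinuation.

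As a minor addition, reword the last sentence of Blinding so that it says who may be unblinded and when, without presuming that the investigator knows the arm. Log any accidental disclosure to the assessor, with date and visit.

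The cost is two sentences and a log entry. Each center already needs a blinded psychologist for the scheduled visits, so no extra staff are required. The sample size and the primary analysis do not change.
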